## 1.0 Specific Aims

Our long-term goal is to promote evidence-based, patient-centered evaluation in the acute setting to more closely tailor testing to disease risk. As PCORI specifies, to “compare the use of risk stratification tools with usual clinical approaches to treatment selection or administration,” we propose the following Aim:

- Test if the decision aid, Head CT Choice, improves validated patient-centered outcome measures and safely decreases healthcare utilization.

Hypothesis: The intervention will significantly increase parents’ knowledge, engagement, and satisfaction, decrease the rate of head CT use, and decrease 7-day total healthcare utilization with no significant increase in adverse events.

## 2.0 Background and Significance

Blunt head trauma is a common cause of death and disability in children worldwide and accounts for approximately 74,000 deaths and 60,000 hospital admissions in the U.S. annually. Each year more than 650,000 children visit U.S. EDs with apparently minor head trauma (Glasgow Coma Scale [GCS] scores of 14-15).

Children with traumatic brain injuries (TBIs) who require acute neurosurgical intervention should be identified rapidly. Cranial CT is the reference standard test for the emergent diagnosis of TBI and is used to identify patients who require acute intervention.

Cranial CT for children with minor head trauma, however, is greatly over utilized. Of the 650,000 children assessed annually for blunt head trauma, approximately 35% undergo head CT. Of these, fewer than 10% have evidence of TBI on CT, and only 0.1% have an intracranial lesion requiring surgical intervention.

Over the past 10 years, CT use has more than tripled both in the U.S. and internationally. Although the benefit to the individual patient can be substantial, cranial CT exposes children to ionizing radiation which has been linked to the development of brain tumors and leukemia. Of the 600,000 cranial and abdominal CT scans performed in U.S. children annually, it has been estimated that 500 might ultimately die from cancer due to CT radiation. Moreover, patients may undergo multiple CT examinations over a lifetime, and the cumulative radiation dose often exceeds the 50 mSv threshold that has been linked to the development of cancer among atomic bomb survivors.

Although there is considerable controversy about the potential risks associated with radiation exposure from CT, all would agree that we should only use as much imaging and radiation as is necessary for patient-centered care and nothing more.

In response to the public health implications of radiation exposure from CT, the

National Cancer Institute has released a guide for health care providers that recommends immediate strategies to minimize CT radiation exposure in children. Different prediction models have been developed to risk-stratify children with minor head trauma. Earlier prediction models are limited by small sample sizes, no external validation, and/or no independent assessment of preverbal children < 2 years of age. [name], [name] (investigators on the current proposal) and colleagues, prospectively derived and validated the Pediatric Emergency Care Applied Research Network (PECARN) clinical prediction rules for cranial CT in children with minor head trauma (one for children < 2 years and a second for children 2-18 years). These prediction rules, which were developed and validated in more than 42,000 children from 25 U.S. EDs, are the most robust prediction models for minor head trauma in children and are sufficiently reliable and accurate to use in practice.

No head injury prediction models, however, were specifically designed to engage the primary stakeholder – the parent/patient dyad – in the decision-making process. The conventional approach to clinical prediction rule development considers the clinician to be the primary decision maker and minimally, if at all, engages patients in decision-making. In the case of CT for minor head trauma, this is particularly troubling because parents are often unaware of their child's risk for a significant TBI, the radiation exposure associated with CT use, and the potential harmful effects of radiation when the decision is made to obtain a cranial CT or to further observe their child. We undertake the first study to intentionally educate and engage parents of children with minor head trauma in the decision making process for head CT.

### **3.0 Preliminary Work**

#### **3.1 Decision Aid Development**

We derived and validated two clinical prediction rules to identify children at very low risk of clinically-important TBIs in more than 42,000 children from 25 U.S. EDs in the PECARN network. In this study we developed 2 prediction rules – one for children < 2 years of age and another for those 2-18 years – that include specific criteria to guide clinicians in deciding whether a CT is necessary, unnecessary or indeterminate based on the presence or absence of several factors such as altered mental status, a history of loss of consciousness, the severity of the mechanism of injury, whether the child is behaving normally according to the parent, or vomiting. These rules identify high-risk children for whom cranial CTs are indicated, middle-risk children for whom either observation or cranial CT are viable options, and very low-risk children for whom cranial CTs can be safely obviated.

We also conducted a systematic review of the literature to identify tools to engage patients in shared decision making (SDM) in the ED to define the state-of-the-art and to identify knowledge gaps. In our review we identified 5 decision support interventions designed to engage ED patients in SDM, three of which were for use in children. Yamamoto and colleagues presented a standardized information sheet that explained the risks and benefits of diagnostic procedures to 37 parents of children at risk for occult bacteremia. In this study 92% of parents expressed a preference to be involved

in the decision-making process, and most decided to forego invasive procedures in their child (e.g., lumbar punctures). In a subsequent study that assessed 45 parents' preferences for sedation for the repair of small lacerations, all 45 parents preferred non-sedation over sedation, and 98% expressed a preference for involvement in decision-making for their child. Finally, Karpas and colleagues assessed parental preferences for rehydration method in children with vomiting and diarrhea. Of the 266 parents who participated in the study, most (62%) preferred intravenous to oral rehydration. *None of these decision support interventions were designed for use in parents of children with minor head trauma.* Overall, these 3 studies indicate that the overwhelming majority of parents prefer to be involved in medical decision-making for their child and that management decisions are sensitive to informed parental preferences.

Based on the above information and with stakeholder (clinicians, parents and experts in shared decision making) involvement, a decision aid for use in parents of children with minor head trauma was developed. The decision aid, *Head CT Choice* (**Appendix 1**), educates parents regarding the definitions of and difference between a concussion and a TBI, how the clinician determined the severity of their child's head trauma, their child's quantitative risk for a clinically-important TBI, the pros and cons of cranial CT compared to active observation, and what signs and symptoms parents should watch for in the next 24 hours that should prompt a return visit to the ED.

### **3.2 Preliminary Studies**

Our preliminary work includes the conduct of a 204-patient single site randomized trial of the *Chest Pain Choice* decision aid in adults presenting to the ED with a primary complaint of non-traumatic chest pain. These patients had no ischemic changes on the initial ECG, negative initial cardiac troponin testing, no history of coronary artery disease, and were being considered for admission and cardiac stress testing within 24 hours (0-6% quantitative pretest probability of ACS within 45 days). Data collection included video-recording of the patient-clinician encounter (degree of patient engagement assessed using the validated OPTION scale), chart review, post-visit patient and clinician surveys, and structured 30-day phone follow-up to assess for a major adverse cardiac event. A patient was considered to have a major adverse cardiac event if they had an acute myocardial infarction, a sustained ventricular dysrhythmia, cardiogenic shock, or death attributed to a cardiac or unknown cause within 30 days of discharge. Compared to usual care, patients in the SDM group had greater knowledge, experienced less decisional conflict related to feeling uninformed as indicated by lower decision conflict scores, and were significantly more engaged in the decision-making process as indicated by higher scores on the validated Option scale (see Table 1). Compared to patients in the control group, patients randomized to the decision aid had a 19% lower rate of admission for cardiac stress testing (58% vs. 77%,  $p < 0.001$ ), a 16% lower rate of cardiac stress testing at 30-days (75% vs. 91%,  $p = 0.002$ ), and there were no major adverse cardiac events after discharge in either group. These preliminary data suggest that SDM is feasible in patients at risk for an emergent diagnosis and that clinicians can effectively engage patients in SDM even in a time-limited acute care environment like the emergency department. For these reasons, we believe engaging

parents of children with minor head trauma in the decision to obtain a head CT is feasible and likely to improve both patient-centered outcomes and healthcare utilization.

**Table 1:** Results from *Chest Pain Choice* single center trial.

| Characteristic                                     | Decision Aid
(n = 101)
N (%) | Usual Care
(n = 103)
N (%) | P-value or
Mean Difference
(95% CI) |
|----------------------------------------------------|------------------------------------|----------------------------------|-------------------------------------------|
| Patient knowledge                           |                                    |                                  |                                           |
| 6 Knowledge Questions                              | 3.6 (3.4, 3.9)                     | 3.0 (2.7, 3.2)                   | 0.67 (0.34, 1.0)                          |
| Correctly assessed 45-day risk for ACS             | 24 (25%)                           | 1 (1%)                           | <.0001                                    |
| Decisional Conflict and Trust               |                                    |                                  |                                           |
| Decisional conflict scale                          | 22.3 (18.1, 26.4)                  | 35.9 (32.2, 39.6)                | -13.6 (-19.1, -8.1)                       |
| Trust in physician                                 | 83.4 (79.4, 87.3)                  | 79.3 (75.4, 83.2)                | 4.1 (-1.4, 9.6)                           |
| Patient participation                       |                                    |                                  |                                           |
| Patient engagement by the clinician (OPTION scale) | 51.4 (49.7, 53.0)                  | 32.0 (31.0, 33.1)                | 19.3 (17.4, 21.2)                         |

## 4.0 Research Design & Methods

### 4.1 Overview

We will conduct a multicenter cluster randomized control trial comparing the efficacy, safety and patient-centered outcomes of the shared decision-making decision aid ‘Head CT Choice’ to usual care among children at low-moderate risk of clinically-important TBI in the ED for whom a CT is being considered to engage parents in shared decision-making.

### 4.2 Overall Schema

[figure not shown]

 – Clinicians will be randomized to usual care or the Head CT Choice decision aid prior to treating an eligible patient. A detailed description of the process by which eligible patients will be identified for inclusion in the study is included in Appendix 2.

## **4.3 Study Setting and Participation**

### **4.3.1 Emergency Department Setting**

The locations include 4 diverse hospital EDs across Minnesota – (1) Mayo Clinic in Rochester, MN (academic ED that serves a largely rural population); (2) University of Minnesota Masonic Children’s Hospital in Minneapolis, MN (academic ED that serves a largely urban population); (3) Children’s Hospital and Clinics of Minnesota, Minneapolis ED; and (4) Children’s Hospital and Clinics of Minnesota, St. Paul ED (2 pediatric community EDs that serve largely urban populations) and 3 hospitals outside the state, (1) University of California Davis Children's Hospital, Sacramento, CA (academic ED that serves a largely urban population) (2) Children’s Nationwide Hospital in Columbus, Ohio (3) Boston Children’s Hospital in Boston, Massachusetts.

#### **4.3.1.1 Eligibility Criteria of Clinicians**

Clinicians caring for children with head trauma.

### **4.3.2 Patient Selection**

Each criterion must be addressed and documented in the patient’s case report form for eligibility assessment prior to randomization. No waivers or exemptions to any eligibility criteria are permitted.

#### **4.3.2.1 Eligibility criteria**

Inclusion:

Parents seeking care for a child who is:

1. < 18 years of age.
2. ≤ 24 hours since injury resulting in head trauma.
3. Moderate risk (0.9%) for clinically-important TBI according to the PECARN prediction rules.

We will exclude parents of children with:

1. GCS scores < 15
2. Evidence of penetrating trauma, signs of basilar skull fracture, or depressed skull fracture on physical examination
3. Brain tumors
4. Ventricular shunts
5. Bleeding disorder
6. Pre-existing neurological disorders complicating assessment
7. Neuroimaging at an outside hospital before transfer
8. Signs of altered mental status (agitation, somnolence, repetitive questioning, or slow response to verbal communication)
9. Syncope or seizure disorder preceded (led to) head trauma or seizure post head trauma
10. Known to be pregnant
11. Communication barriers such as visual or hearing impairment that may preclude use of the decision aid.

12. Strong suspicion of abuse for this head injury

#### 4.4 Registration/Randomization Procedures

The flow and process of identifying eligible patients for enrollment in the study is depicted in **Appendix 2**.

Given the relatively limited number of pediatric clinicians at each site and the great degree of familiarity with the PECARN head CT decision rules across the specialty of pediatric emergency medicine, randomizing at the patient level is associated with a significant risk of contamination of the intervention. As such, we will randomize at the clinician level to limit contamination.

Informed consent will be obtained from clinicians at each site prior to enrollment of that clinician's parent/child dyad. After clinician consent is completed, the site study coordinator will contact the statistical team ([[name]/[name]](#)) with enrollment information via email. The statistician will centrally randomize the clinician and communicate that to the site principle investigator and study coordinator.

Informed consent will also be obtained from the parent/guardian of a child with minor head trauma. The parent must provide signed and dated consent for the use of their Protected Health Information (this may be incorporated into the informed consent document). Prior to registering a parent(s) to the study, all of the eligibility criteria on the eligibility checklist must have been met. **No waivers or exemptions to any eligibility criteria are permitted.** All eligibility criteria must be fully documented on the case report form and subsequently entered into the study database.

#### 4.5 Intervention

Parents/Guardians in the intervention group will discuss testing to diagnose their child's head injury with their clinician, facilitated by use of the Head CT Choice decision aid.

##### 4.5.1 Head CT Choice Decision Aid (**Appendix 1**)

For patients whose clinician is randomized to the decision aid arm:

1. The study coordinator, using the PECARN risk estimates, will select the correct pre-printed and individualized decision aid for the parent/clinician dyad.
2. The study coordinator will provide a color-printed copy of the decision aid to the clinician prior to the clinician having the head CT discussion with the parents.
3. The study coordinator will offer to provide the treating clinician a concise refresher of the content included in the decision aid in the context of the trial.
4. The clinician will then, using the decision aid as a tool to facilitate discussion, educate the parents regarding the difference between a

372 concussion and a traumatic brain injury, how the clinician determined the  
373 severity of their child's head trauma, their child's quantitative risk for a  
374 clinically significant brain injury, the pros and cons of head CT compared to  
375 active observation, and what signs and symptoms parents should watch for in  
376 the next 24 hours that should prompt a return visit to the ED.

- 377 5. The clinician will then engage the parents in a shared decision regarding the  
378 option of head CT versus active observation and come to a decision that is  
379 consistent with both the parent's values and preferences and the clinician's  
380 level of comfort.

#### 381 382 4.5.1.1 Training of Personnel 383

384 Study personnel from the central site will conduct a 1 hour grand rounds presentation  
385 and do a demonstration in the use of the decision aid during in-person visits with  
386 participating sites. Study personnel may also provide a reminder of how to use the  
387 decision aid as needed or in response to deviations in the quality of delivery observed  
388 on video recordings. Brief video clips that demonstrate the basic use of decision aid  
389 will be provided to clinicians to review at their convenience. Designated site staff will  
390 receive training in the consenting procedures prior to actually consenting patients.

#### 391 4.5.2 Usual Care 392

393 For parents whose clinician is randomized to the usual care arm, the clinician will  
394 discuss management options with the parent in the clinician's usual fashion. The  
395 clinician-parent discussion will be video-recorded, and immediate post-visit surveys to  
396 the patient and clinician administered. Patients in the usual care arm will also be  
397 contacted at 7 days to assess the study outcome measures.

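### Training in the decision aid is not restricted to clinicians allocated to it, so usual-care clinicians may be exposed to the intervention

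*Protocol*

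**What the plan says.** Section 4.4 (Registration/Randomization Procedures) gives the reason for the clustered design. Because each site has few pediatric clinicians, "randomizing at the patient level is associated with a significant risk of contamination of the intervention", and the protocol concludes: "As such, we will randomize at the clinician level to limit contamination".

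Section 4.5.1.1 (Training of Personnel) sets out how the aid is taught:

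- Grand rounds: "Study personnel from the central site will conduct a 1 hour grand rounds presentation".
- Demonstration, in the same sentence: "and do a demonstration in the use of the decision aid during in-person visits with" the participating sites.
- Clips: "Brief video clips that demonstrate the basic use of decision aid" "will be provided to clinicians to review at their convenience".
- Reminders: study personnel may remind clinicians how to use the aid, as needed or when recordings show lapses in delivery.

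None of these sentences says which arm the recipients belong to. Section 4.5.2 (Usual Care) neither offers this training to usual-care clinicians nor keeps them from it.

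**The concern.** The trial accepts the cost of clustering to keep usual-care clinicians from picking up the intervention. The intervention is largely what the clinician explains and how the parent is drawn into the choice (section 4.5.1, steps 4 and 5), so a clinician who has watched a demonstration can reproduce part of it without the printed sheet. Grand rounds and site-visit demonstrations are site-wide formats. Unless the protocol separates the arms, they can reach both.

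If usual-care conversations moved toward the intervention, the differences in knowledge, engagement and head CT use would shrink toward zero while the trial still paid the clustering penalty. Analysis cannot undo this, and exposure cannot be reversed once it has happened.

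**Working it through.** **1. The text.** The question is whether any provision limits the training by arm.

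| Provision | Protocol section | Tied to the decision-aid arm? |
|---|---|---|
| Printed, individualised aid | 4.5.1, steps 1–2 | Yes |
| Coordinator's refresher | 4.5.1, step 3 | Yes |
| Grand rounds | 4.5.1.1 | Not stated |
| Demonstration at site visits | 4.5.1.1 | Not stated |
| Video clips | 4.5.1.1 | Not stated; addressed to clinicians |
| Reminders by study personnel | 4.5.1.1 | Not stated, though they presuppose someone delivering the aid |

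Two features of section 4.8.4 make the gap matter. Randomisation is stratified by site, so both arms share a department. Clinicians may also be randomised when they first treat an eligible patient, so one could attend a demonstration with no allocation and then be assigned to usual care.

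**2. Illustration of size.** The documents give no contamination rate. Let c be the assumed share of usual-care encounters that take on the full effect of the aid.

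Inputs from section 4.8.3: head CT 49% v 34%, stated power 95%; trust difference 4.1 with SD 20, stated power 86%; knowledge 44% v 60%, stated power above 99%; 950 patients, about 75 clinicians, up to 5% loss, two-sided alpha 0.05. Evaluable: 950 × 0.95 ≈ 902, or n = 451 per arm.

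Formula for head CT: p₁ = 0.49 − 0.15c, p₂ = 0.34, d = p₁ − p₂, p̄ = (p₁ + p₂)/2, and

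power = Φ[(d − 1.96·√(2p̄(1−p̄)/n)) / √((p₁(1−p₁) + p₂(1−p₂))/n)].

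*Reproducing the stated figures (c = 0).* Without clustering, head CT: (0.15 − 1.96 × 0.03281)/0.03243 = 2.64, power 99.6%, against 95% stated. The stated 95% corresponds to an effective n of about 277.5 per arm, a design effect of 451/277.5 ≈ 1.63 (or 475/277.5 ≈ 1.71 if all 950 are counted). With about 12 to 13 patients per clinician this is an intraclass correlation near 0.06, a value the section does not state. Trust without clustering: standard error 20·√(2/451) = 1.332; Φ(4.1/1.332 − 1.96) = 86.8%, which matches the stated 86% within rounding.

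*With contamination.* Example at c = 20%: p₁ = 0.46, d = 0.12, p̄ = 0.40. At n = 277.5: (0.12 − 1.96 × 0.04159)/0.04128 = 0.93, power 82%.

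| Assumed c | Head CT difference (points) | Power at implied design effect | Power without clustering | Trust power, no clustering |
|---|---|---|---|---|
| 0 | 15.0 | 95% | 99.6% | 87% |
| 10% | 13.5 | 90% | 99% | 79% |
| 20% | 12.0 | 82% | 96% | 69% |
| 30% | 10.5 | 72% | 90% | 58% |

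For knowledge, the primary outcome, the 16-point difference would shrink to 16 × (1 − c) = 14.4, 12.8 or 11.2 points. With stated power above 99%, the main harm there is an underestimated effect rather than a missed one.

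**The case against.** The strongest reply is placement. Section 4.5.1.1 sits under 4.5.1, which opens "For patients whose clinician is randomized to the decision aid arm", while usual care has its own section with no training in it. On that reading the training belongs to the aid arm. This has some force but is not a dependable restriction: the opening line introduces the five encounter steps, and 4.5.1.1 also covers consent training for site staff, which both arms need.

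Other points stand:

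- The content of the grand rounds is not described; only the demonstration and the clips are said to show use of the aid.
- The printed aid and the coordinator's refresher go only to the aid arm.
- Clinicians are mainly randomised at the start, so training after allocation is compatible with the plan.
- The fidelity checklist in 4.7.2 covers recordings in both arms. It can detect contamination but not prevent it, and only in recorded encounters, since recording may be declined (4.7).

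A reader might infer that usual-care clinicians will be taught the aid, or that the training brings back the contamination which clinician-level randomisation was meant to avoid. The protocol supports neither. It is silent on who attends, and the design still prevents one clinician from using the aid with some parents and then seeing control parents. Watching a demonstration is also a weaker exposure than repeated use.

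**Conclusion.** The concern holds as a gap with a plausible consequence. Section 4.5.1.1 uses site-wide formats without restricting them by arm, in departments that hold both arms and where some clinicians have no allocation yet. Followed as written, it may expose usual-care clinicians and work against the purpose given in 4.4. The expected direction is toward no difference.

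The size cannot be established from the protocol. The power figures rest on assumed contamination shares, on a contaminated encounter gaining the full effect without the printed aid, and, for the clustered column, on a design effect back-solved from the stated 95%. They illustrate how much could be lost and are not an estimate. The change should be made because it is cheap and has to come before training begins.

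**What to change.** In section 4.5.1.1:

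1. State who attends each training activity and when, relative to allocation.
2. Give the demonstration of the aid, the video clips and the study-personnel reminders only to clinicians already allocated to the decision-aid arm. The coordinator's refresher in 4.5.1 step 3 is already arm-specific and needs no change.
3. Limit site-wide sessions, including grand rounds, to trial procedures such as screening, consent, surveys and recording, without the aid.

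In section 4.7.2, state that the fidelity checklist will be reported for usual-care recordings as a measure of contamination, with the number of encounters recorded.

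The cost is about one paragraph of text and a separate session for aid-arm clinicians at each visit, with slightly more scheduling, including for those allocated late. Sample size, endpoints and analysis are unaffected.
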